## 2. Materials and Methods

This is a randomized, double-blind, crossover, and sham-controlled study. A crossover design has been chosen, so that each participant can act as his or her own control in an attempt to limit the inter-subject variability. In addition, such a design requires a smaller sample size compared to a parallel group design for the same statistical power [39]. However, one should acknowledge the limitations of this within-subject design, mainly, the time burden imposed on patients (longer participation time compared to the parallel-group design), and the possibility of a carry-over effect (e.g., potential neuroplastic effects induced by the preceding tDCS effects) or an order effect. The former effect cannot be formally ruled out, but was taken into consideration by including a washout period of 3 weeks between tDCS blocks, as done previously [40]. The latter effect could be controlled by counterbalancing the tDCS order among patients and could be statistically tested by adding the order as a covariate in the analysis of covariance (ANCOVA).

The study was approved by the institutional review board of the Lebanese American University, Lebanon (IRB registration #IRB00006954). All patients will voluntarily give their written informed consent prior to inclusion. The study will take place in conformity with the Declaration of Helsinki and its amendments.

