### 2.3. Sample Size, Randomization and Blinding Effectiveness

In the absence of published data on this topic, the statistical outcomes of this study can serve in understanding and guiding the therapies of altered dexterity in MS patients. Previous tDCS studies addressing dexterity in stroke patients adopted sample sizes between 10 and 19 and yielded statistical significance [59,60].

In the absence of sham-controlled studies on this matter, sample size calculation was performed using the G*Power Software (version 3.1.9.6 [61]). A 2 × 3 within-subjects repeated measures analysis of variance was considered, with the factor time (before and after each stimulation condition) and the factor stimulation condition (active cathodal cerebellar, active anodal motor vs. sham). Considering the predicted medium effect size (f = 0.25) and adopting a two-tailed significant difference of α = 0.05 and an estimated power of 80%, the sample size estimate is 36. Taking into consideration a dropout rate of up to 25%, a sample of 45 patients will be sufficient to observe significant effects. *N* = 48 was adopted to be able to counterbalance the order of conditions as will be explained below.

Randomization will be performed by a researcher who will not be in contact with patients. In the first step, six different sets of blocks will be assigned, and each contains four patients: (active cathodal cerebellar, sham, active anodal motor), set B (active cathodal cerebellar, active anodal motor, sham), set C (sham, active cathodal cerebellar, active anodal motor), set D (sham, active anodal motor, active cathodal cerebellar), set E (active anodal motor, sham, active cathodal cerebellar), and set F (active anodal motor, active cathodal cerebellar, sham). In the second step, each set will be split into two subsets according to the sham setup, so that two patients per set will receive sham over the motor cortex (setup similar to active condition), and the other ones will receive sham over the cerebellum (setup similar to active condition). The flow chart of the protocol is displayed in Figure 2. The evaluators will assess the patients before and after tDCS blocks and will be blind to the stimulation conditions. Patients will be blind to the stimulation condition.

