### 2.9. Statistical Analysis

The statistical analysis will be performed using the SPSS software (IBM Corp. Released 2016. IBM SPSS Statistics for Windows, Version 24.0. Armonk, NY: IBM Corp). The primary and secondary outcomes will be analyzed using the same statistical approach. For all variables, the normality of data distribution will be tested using the Kolmogorov–Smirnov test. The homogeneity of variance will be tested using the Levene’s test. Depending on the data distribution, the scores obtained before and after all tDCS conditions will be compared using the repeated measures analysis of variance (ANOVA) or the Friedman test under six conditions: 2 times (before and after tDCS) × 3 stimulation conditions (anodal motor tDCS, cathodal cerebellar tDCS, and sham). When appropriate, the post hoc Dunn’s test will be applied. Two-tailed p-values less than 0.05 will be considered significant. Data will be presented as the mean ± the standard deviation or the median (1st and 3rd quartiles).

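### Section 2.9 names Levene's test as the variance check for a wholly within-patient ANOVA, where the assumption that matters is sphericity; the possible error inflation is small and conditional

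*Protocol article*

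**What the plan says.** Section 2.9 (Statistical Analysis) names two assumption checks: Kolmogorov–Smirnov for normality and, for variances, "The homogeneity of variance will be tested using the Levene’s test". The scores before and after stimulation "will be compared using the repeated measures analysis of variance (ANOVA) or the Friedman test under six conditions", set out as "2 times (before and after tDCS) × 3 stimulation conditions (anodal motor tDCS, cathodal cerebellar tDCS, and sham"). The choice between ANOVA and Friedman depends on the data distribution. The threshold is: "Two-tailed p-values less than 0.05 will be considered significant". Primary and secondary outcomes follow the same approach.

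Section 2.3 sizes the trial on the same model: "A 2 × 3 within-subjects repeated measures analysis of variance was considered". Section 2 gives the reason for the crossover, that "each participant can act as his or her own control". The only between-patient term raised for analysis is treatment order, which section 2 says "could be statistically tested by adding the order as a covariate in the analysis of covariance (ANCOVA"). Section 2.9 does not carry it into its model. The article mentions neither sphericity nor a correction for departures from it.

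**The concern.** Levene's test assumes that the groups being compared are independent. In the model of section 2.9 every patient supplies all six scores, so running the test across those scores would treat correlated measurements from the same people as independent.

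The condition effect and the time × condition interaction each have 2 degrees of freedom. Their F tests are exact only if the differences between conditions (for the interaction, differences between the before-to-after changes) all have the same variance. That is sphericity, and it depends on correlations as well as variances. Even a variance test suited to paired data would therefore check only part of it.

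The interaction is the test that asks whether the conditions differ in their effect on the 9-HPT. If response varies more under one condition, or two conditions give more strongly correlated responses than the third, the uncorrected F test rejects too often.

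This goes beyond detail left to a fuller document. The article does name a variance check, and it names one that does not fit its own model.

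**Working it through.** **Inputs from the article.** Time (2 levels) × condition (3 levels), both within patient; two-tailed α = 0.05; f = 0.25; power 80%; 36 evaluable patients; 48 recruited. At the stated worst dropout of 25%, 48 × 0.75 = 36, so N = 36 and N = 48 bracket the analysed sample.

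**Inputs not in the article (assumed).** SDs of the within-patient changes and the correlations between them. A range is shown.

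**The plan's own figure.** For within-patient factors, λ = f²·N·m·ε/(1 − ρ), df1 = (m − 1)ε, df2 = (N − 1)(m − 1)ε. With m = 6, ρ = 0 and ε = 1, the smallest N reaching 80% power is 36, with λ = 0.0625 × 36 × 6 = 13.5 on 5 and 175 df. With ε = 0.75 or 0.5 and the rest unchanged, N is 43 or 57. The match is not unique (m = 3, ρ = 0.6, ε = 0.5 also gives 36), so the stated 36 does not show what was assumed about sphericity.

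**Size of the departure.** Take the three before-to-after changes per patient, with contrasts (1, −1, 0)/√2 and (1, 1, −2)/√6. In the patterns below the contrasts are uncorrelated, with variances v1 and v2, and

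ε = (v1 + v2)² / [2(v1² + v2²)].

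- Independent changes with SDs 1, 1, r: v1 = 1 and v2 = (1 + 2r²)/3. For r = 2, v2 = 3 and ε = 16/20 = 0.80. For r = 3, v2 = 6.33 and ε = 0.65.
- Equal variances, correlation 0.8 between the two active conditions and 0 with sham: v1 = (2 − 1.6)/2 = 0.20, v2 = (2 + 1.6 + 4)/6 = 1.27, ε = 0.65.

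**False-positive rate of the 2-df interaction test, no true mean difference.** Normal changes were simulated. Rows with both sample sizes used 100,000 runs and the others 40,000 (simulation standard error about √(0.05 × 0.95/40,000) = 0.1 percentage point).

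| Pattern of changes | ε | Uncorrected, N = 36 | Uncorrected, N = 48 |
|---|---|---|---|
| Equal SDs, spherical | 1.00 | 5.1% | 5.1% |
| One SD 1.25 times | 0.98 | – | 5.1% |
| One SD 1.5 times | 0.92 | – | 5.4% |
| One SD 2 times | 0.80 | 6.0% | 6.1% |
| One SD 3 times | 0.65 | 7.0% | 7.1% |
| One SD 4 times | 0.59 | – | 7.5% |
| Equal variances, correlations 0.8, 0, 0 | 0.65 | 7.0% | 7.1% |
| Lower bound | 0.50 | 8.6% | 8.5% |

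The last row is a calculation: P[F(1, N − 1) > F0.95(2, 2(N − 1))]. The Greenhouse-Geisser corrected test stayed between 4.7% and 5.1% in every pattern simulated.

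The equal-variance row shows that a check confined to variances misses a departure as damaging as a threefold SD ratio.

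**Cost of the correction.** Under sphericity, with sham shifted so that the uncorrected test had 80% power, the corrected test had 79.4% at both N = 36 and N = 48 (100,000 runs each).

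**The case against.** **The harm comes from an omission.** Naming Levene's test inflates nothing; only leaving out a correction does, and an article may leave that to a fuller plan. This stands in part. Nothing in section 2.9 rules out a correction, and the unseen plan may apply one. The stated check is still the wrong one for the stated model.

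**Between-patient groups do exist.** Section 2.3 creates six sequences and two sham-site subsets, and section 2 allows order as a covariate. Levene's test could serve there. But section 2.9 enters none of these, so this limits the fix and does not remove the point.

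**Counterbalancing protects the strict null.** If stimulation does nothing in any patient, balanced sequences make the three changes exchangeable. Simulation with period SDs differing two- to threefold (N = 48, 40,000 runs) gave 4.6–5.0% uncorrected. Inflation therefore needs stimulation to alter the spread or correlation of responses while leaving the means equal. This is correct, and it narrows the concern. It also means that splitting sham between two sites adds no variance if sham is inert.

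**Stronger readings that the article does not support.**

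- A reader might infer that a Levene result would steer the analysis to the uncorrected p-value. Section 2.9 attaches no decision to that result; its only branch, on data distribution, chooses between ANOVA and Friedman.
- A reader might infer that inflation would go unnoticed. Repeated measures software may print corrected p-values anyway; the article simply does not say which one counts.
- A reader might infer that every secondary outcome is affected. Outcomes sent to Friedman are not, and ordinal grades such as MAS, MRC and ataxia scores are plausible candidates. The primary outcome could take that route too.

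Section 3 also calls the study exploratory, which lowers the stakes.

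**Conclusion.** The point holds in limited form: the named variance check does not fit the within-patient model, and the assumption that does matter is left unaddressed.

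The consequence applies only to ANOVA tests involving the three-level stimulation factor, and only if uncorrected p-values are used. The excess is then about half a percentage point or less for SD ratios up to 1.5, about 1 point at 2, about 2 points at 3, and at most about 3.6 points (8.6% against 5%). The SD ratios and correlations are assumptions, and the excess is zero under sphericity. This is a minor correction and does not threaten the trial's conclusions.

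**What to change.** In section 2.9, replace the Levene sentence with: *Greenhouse-Geisser corrected p-values will be used for all ANOVA tests involving the three-level stimulation factor.* Keep Levene's test only if a between-patient factor, such as sequence, is entered in the model, and say that this is its purpose. If a mixed model is used instead, an unstructured covariance across conditions serves the same end.

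The change costs one sentence, needs no new data, and loses about 0.6 of a percentage point of power (80% to 79.4%) when sphericity holds. It should be made before the data are analysed.

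### The ANOVA branch tests treatment on raw D5 minus D1 changes, without a period term and in complete patients only, and can discard information that a mixed model on the same data keeps

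*Protocol article*

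**What the plan says.** Section 2.9 applies one approach to all outcomes. Depending on the distribution, "the scores obtained before and after all tDCS conditions will be compared using the repeated measures analysis of variance (ANOVA") or by the Friedman test, over two times and three stimulation conditions, with sham as a single level. The section also states: "The homogeneity of variance will be tested using the Levene’s test". It names no period, order or sham-site term and no baseline covariate.

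Section 2 mentions order effects. It relies on counterbalancing and adds that order "could be statistically tested by adding the order as a covariate in the analysis of covariance (ANCOVA"). Section 2.9 does not take this up.

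Section 2.3 plans on the same layout, a "within-subjects repeated measures analysis of variance was considered, with the factor time (before and after each stimulation condition") and the factor condition. It uses all six orders, allows for up to 25% dropout and recruits 48. It splits each order set by sham site: "two patients per set will receive sham over the motor cortex (setup similar to active condition"), and the others receive it over the cerebellum. Section 2.5 has the 9-HPT measured on D1 and at the end of D5 in every block.

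**The concern.** In a 2 × 3 within-patient ANOVA, treatment is tested by the time-by-condition interaction, which is a comparison of D5 minus D1 across conditions. The D1 value is therefore used only by subtraction, with its slope forced to 1. If D1 and D5 in a block are imperfectly correlated once the patient's own level is removed, subtraction adds noise that regression on D1 would not.

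Two further features cost information. First, a shift between blocks, from practice for example, goes into the error term because period is not fitted. The order covariate in Section 2 cannot replace it: order labels the patient's sequence, whereas period labels the block within the patient. Second, classical repeated measures ANOVA needs all six cells, so a patient with two completed blocks contributes nothing.

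Levene's test compares variances between independent groups, and this comparison has none.

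At stake is precision in a trial that plans on only 36 complete patients.

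**Working it through.** **The plan's own figure.** Section 2.3 gives "predicted medium effect size (f = 0.25"), "adopting a two-tailed significant difference of α = 0.05", and "an estimated power of 80%, the sample size estimate is 36". Correlation, sphericity and the tested term are not stated. With assumed correlation 0.5 and ε = 1, and λ = N·f²·m·ε/(1 − ρ):

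- m = 2, one group: N = 34; with 3 or 6 groups, rounded to equal groups: N = 36.
- m = 3, one group: 28. m = 6, one group: 19.

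So 36 can be reproduced, though the settings behind it are unclear. 36 × 1.25 = 45 and 36/(1 − 0.25) = 48, so the adopted 48 leaves 36 complete patients at 25% dropout.

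**Change scores against adjustment for D1.** Let v be the variance of a measurement around the patient's mean, and x the D1–D5 correlation within a block on that scale. Per patient, for active minus sham:

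- change scores: 4v(1 − x)
- D5 adjusted for D1: 2v(1 − x²)
- ratio: (1 + x)/2, so the information lost is (1 − x)/2.

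In raw correlations, rw within a block and rb between blocks, x = (rw − rb)/(1 − rb). Two assumed examples:

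- rw 0.90, rb 0.85: x = 0.33, ratio 0.667, so 36 patients act like 36/0.667 = 54.
- rw 0.90, rb 0.60: x = 0.75, ratio 0.875, so 36 patients act like 36/0.875 = 41.

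If all six measurements share one common correlation, rw = rb, x = 0 and half the information is lost.

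**Adding dropout.** Assume 48 enrolled, 6 leaving after block 1 and 6 after block 2. Completer change scores were compared with generalised least squares on all D1 and D5 data, with period effects, a D1 mean common to the conditions, and patient, patient-by-block and residual variances (patient ICC 0.5; 0.7 and 0.9 differ by at most 0.5 points).

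| x | Loss, no dropout | Loss, 25% dropout, half and half |
|---|---|---|
| 0.9 | 5% | 18% |
| 0.8 | 10% | 23% |
| 0.7 | 15% | 27% |
| 0.5 | 25% | 35% |
| 0 | 50% | 56% |

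With this dropout the loss reaches a quarter at x of about 0.74 or less. The threshold is about 0.65 if all 12 leave after block 1 and about 0.83 if all leave after block 2.

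The dropout column assumes that patients do not differ in their underlying change, so that comparisons between patients also carry information. As a cautious check, count within-patient information only. A two-block patient is then worth half a complete one and a one-block patient nothing: 36 against 36 + 6/2 = 39. The loss is 1 − [(1 + x)/2](36/39): 12% at x = 0.9, 31% at 0.5 and 54% at 0.

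**Period.** Suppose the mean change in block 1 is shifted by a standard deviations of change. The error variance is then inflated by 1 + a²/3, a loss of 2%, 8% or 25% at a = 0.25, 0.5 or 1. With the six orders equally filled, each condition occurs equally often in each block, so the contrasts are not biased.

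**The case against.** The strongest reply is that the size of the loss is not in the document. Neither the correlations nor the timing of dropout is given, and 25% is an upper limit, not an expectation. D1 is also not a single noisy reading: Section 2.4.1 sums five recorded trials after five training trials, which may raise x and will blunt practice effects. All of this stands. A reader might infer that at least a quarter of the information is certainly lost; the documents do not support that, because at x = 0.9 the loss is 5% without dropout and about 18% with it.

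A second reply is that this is a condensed article, so missing-data rules, sphericity corrections and sham-site terms may sit elsewhere. That is fair for those details, and deletion of incomplete patients is indeed inferred from the named method, not written. It does not cover the choice of model and factors, which Section 2.9 fixes.

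A third reply is that balanced orders deal with period. They do so for bias, not for precision. Uneven dropout could unbalance the orders, but nothing in the documents says that it will.

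A reader might also infer that carry-over favours active stimulation. Sham follows an active block in 4 of 6 orders, and each active condition follows the other in 2 of 6. A residual effect c at D1 therefore shifts the active-minus-sham change by (4 − 2)/6 = c/3, but only if it is present at D1 and gone by D5. If it persists to D5, change scores cancel it, and the D1-adjusted model removes only part of it.

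**Conclusion.** The point holds as a matter of efficiency. The stated ANOVA uses each D1 value less well than it could, leaves period in the error and, by its nature, excludes incomplete patients. The loss is (1 − x)/2 without dropout. At the full 25% dropout, split evenly after blocks 1 and 2, it runs from about 18% (x = 0.9) to about 56% (x = 0), or 12% to 54% on within-patient information alone. These figures rest on an assumed x, an assumed dropout pattern and no carry-over into the next D1. In the generalised least squares calculations the mixed model was never less efficient.

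The documents do not establish biased condition contrasts or a fixed loss of a quarter. Nor do they show that the plan misses its own target, since 48 less 25% leaves the 36 that it asks for. Sham site and sphericity are secondary and could be settled in a separate analysis plan. Levene's test is simply out of place. This is a worthwhile, inexpensive improvement and not a fatal flaw.

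**What to change.** In the ANOVA branch of Section 2.9, make the primary analysis a linear mixed model of the D5 value. Fixed effects: condition, period (1–3), the block's D1 value and the patient's mean D1 value. Random effect: patient. Use all completed blocks. The primary contrasts are each active condition minus sham.

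Keep the change-score ANOVA as a sensitivity analysis with Greenhouse–Geisser p-values. Fit first-order carry-over and sham site as further sensitivity terms. Delete Levene's test.

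The cost is analysis wording and a little more programming; all the data are already collected. There is one statistical downside. If a residual effect persists from D1 to D5, the D1-adjusted model removes it only partly, whereas change scores cancel it. That is the reason to keep the change-score analysis as a check.

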## Abstract

Background: Cerebellar and motor tracts are frequently impaired in multiple sclerosis (MS). Altered hand dexterity constitutes a challenge in clinical practice, since medical treatment shows very limited benefits in this domain. Cerebellar control is made via several cerebellocortical pathways, of which the most studied one links the cerebellum to the contralateral motor cortex via the contralateral ventro-intermediate nucleus of the thalamus influencing the corticospinal outputs. Modulating the activity of the cerebellum or of the motor cortex could be of help. Method: The main interest here is to evaluate the efficacy of transcranial direct current stimulation (tDCS), a noninvasive brain stimulation technique, in treating altered dexterity in MS. Forty-eight patients will be recruited in a randomized, double-blind, sham-controlled, and crossover study. They will randomly undergo one of the three interventions: anodal tDCS over the primary motor area, cathodal tDCS over the cerebellum, or sham. Each block consists of five consecutive daily sessions with direct current (2 mA), lasting 20 min each. The primary outcome will be the improvement in manual dexterity according to the change in the time required to complete the nine-hole pegboard task. Secondary outcomes will include fatigue, pain, spasticity, and mood. Patients’ safety and satisfaction will be rated. Discussion: Due to its cost-effective, safe, and easy-to-use profile, motor or cerebellar tDCS may constitute a potential tool that might improve dexterity in MS patients and therefore ameliorate their quality of life.

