### 2.4. Description of the Clinical Evaluation

#### 2.4.1. Primary outcome: hand dexterity

The Nine-Hole Peg Test (9-HPT) will be administered by the evaluating physician to assess hand dexterity [5,62,63]. Briefly, patients will be trained to perform the test for five consecutive trials. The inter-trial interval will be 1 min. For each trial, the subject begins with the hand resting beside the pegboard. The experimenter initiates the trials with a verbal ready–steady–go command, and times the trial with a digital stopwatch. After training trials, another five trials will be done, recorded, and their sum will be calculated.

The dependent variable is the number of pegs per second computed based on nine pegs placed compared to the time needed to finish the test [63]. In case of inability to complete the test, the variable corresponds to the number of pegs placed divided by the time limit of the test (300 s).

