### 2.5. Experimental Protocol

The first visit is an inclusion visit, where the examining physician will perform the neurologic exam, and verify the inclusion and exclusion criteria. Patients will obtain information regarding the protocol, consent form, and the other questionnaires to be filled. They will be called in the following days to check if he/she agrees to participate in the study and therefore to plan the stimulation sessions. In case of acceptance, an appointment will be scheduled in order to sign the consent form and deliver a booklet containing the VAS for pain to be filled for one week prior to the stimulation week and during the week of stimulation. If present, medications and physical therapy will be kept the same as the previous month. Patients will be asked to restrict stimulant consumptions (e.g., caffeine, nicotine) at least three hours prior to their appointments.

Each patient will be randomly assigned to receive 3 blocks separated by a washout interval of three weeks (anodal tDCS over M1 contralateral to the most affected hand, cathodal tDCS over the cerebellum, and sham over either cortical site). Each block will consist of five 20-min stimulation sessions, applied on day 1 to day 5 (D1 to D5). On D1, dexterity will be quantified based on the time required to perform the 9-HPT. Each patient will be evaluated for fatigue (MFIS), anxiety and depression (HADS), spasticity (MAS), motor power (MRC), and cerebellar function (ataxia scale). Afterwards, tDCS will be performed in a quiet and well-illuminated room with the patient sitting in an armchair without any concurrent cognitive or motor task. The stimulation session will be repeated from D1 to D5. At the end of D5 session, each patient will undergo the same evaluation as done on D1 (9-HPT, MFIS, HADS, MAS, MRC, ataxia scale), as well as the CRQ, CGI, and will be delivered a VAS booklet (pain) to be filled for one week following D5 and for one week prior to the next tDCS block. 

Each patient will be included in the study for 3 months. 2 patients per week will undergo the stimulation block. The study will take place for a total duration of 12 months, and the final data analysis will be performed in less than a year. The schematic diagram of the protocol is illustrated in Figure 3. 

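### On the non-normal branch, one Friedman test across all six time-by-condition cells can be significant from a gain shared with sham, so it does not test whether active stimulation changes dexterity more than sham.

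*Protocol article*

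**What the plan says.** The abstract of the protocol article defines the primary outcome as the "improvement in manual dexterity according to the change in the time required to complete the nine-hole pegboard task". Section 2.5 places the assessments at the start and end of each block: "At the end of D5 session, each patient will undergo the same evaluation as done on D1". Each of the three blocks (anodal motor, cathodal cerebellar, sham) thus yields a before and an after score.

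Section 2.9 lets the data choose the method: "Depending on the data distribution, the scores obtained before and after all tDCS conditions will be compared" by repeated-measures ANOVA or by "the Friedman test under six conditions: 2 times (before and after tDCS) × 3 stimulation conditions". The follow-up is given in one sentence, "When appropriate, the post hoc Dunn’s test will be applied", without naming the pairs or an adjustment. The decision rule is "Two-tailed p-values less than 0.05 will be considered significant". The scope is wide: "The primary and secondary outcomes will be analyzed using the same statistical approach".

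Section 2.9 names neither a change score nor a time-by-condition contrast for the Friedman branch.

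**The concern.** The trial asks whether the D1-to-D5 change differs between active stimulation and sham. A Friedman test on six columns asks whether any of the six cells differs from any other. The two questions part company when patients improve within every block, sham included: the six-cell null is then false although stimulation has done nothing.

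A shared gain is plausible. The same timed task is repeated at the start and end of each block, and a placebo response would also appear under sham. If the omnibus p-value, or a before/after pair within an active block, is read as efficacy, the 5% rule does not control false positives for the treatment question. The normality check on the trial's own scores also decides whether the hypothesis tested contains the treatment comparison at all.

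**Working it through.** **Inputs from the article.** Six cells (2 times × 3 conditions), two-sided 0.05, Dunn's test as follow-up (section 2.9). Six counterbalanced orders, a sample size estimate of 36 and 48 patients adopted (section 2.3).

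**The plan's own figure.** The 36 for f = 0.25 and 80% power is reproduced with one group, six measurements and a correlation of 0. Other settings also give 36, and the article does not state its settings, so this does not show which test was powered. It serves here only to fix the two sizes, n=36 and n=48.

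**The test as written.** With k = 6 cells and mean ranks R̄j, Q = [12N / (k(k+1))] Σ(R̄j − 3.5)² = (12N/42) Σ(R̄j − 3.5)², referred to chi-square on k − 1 = 5 degrees of freedom. A gain common to all blocks moves the three after-ranks up and the three before-ranks down (or the reverse, depending on scoring), so Q grows with the gain. No term compares one block's change with another's. Dunn's follow-up has 6 × 5 / 2 = 15 pairs of cells, and none is a difference between two changes.

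**Simulation with no stimulation effect.** Assumed: between-patient SD 2, block SD 0.5, within-assessment SD 1 (the unit of the gain), and the same gain in all three blocks.

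| Shared gain (within-patient SD) | Six-cell Friedman rejects, n=36 | n=48 |
|---|---|---|
| 0 | about 5% | about 5% |
| 0.1 | about 7% | about 7% |
| 0.25 | about 17% | about 23% |
| 0.5 | about 66% | about 80% |
| 0.75 | about 97% | about 99% |

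Repeat runs agreed to within about three percentage points. Friedman on the three within-block changes stayed at 4% to 6% throughout, and the ANOVA interaction F at 4.5% to 5.6%.

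**Dunn's pairs.** With Bonferroni over 15 pairs (0.05/15 = 0.0033) and a shared gain of 0.5 SD, a before/after pair is significant in at least one active condition, while the sham pair is not, in about 17% (n=36) to 25% (n=48) of null trials. The active-after versus sham-after pair is not inflated: for one such pair, unadjusted and taken after a significant omnibus test, the rate was 1.3% to 4.8%. With Bonferroni it was below 1%.

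**Sensitivity to skewness and correlation.** With lognormal scores and the gain in SD of the log score, a gain of 0.2 gave rejection in 33% (correlation 0.5), 74% (0.8) and 98% (0.9) at n=48, and in 25% to 91% over the same correlations at n=36. At correlation 0.8 the within-patient SD is √0.2 = 0.447, so 0.2 is 0.2/0.447 = 0.45 within-patient SD, in line with the table. Friedman on the three changes stayed at 4.6% to 6.3%. A pure block-to-block trend of 0.2 SD per period, with no within-block gain, gave 1% to 4%: counterbalancing deals with that.

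**The case against.** The strongest reply is that the post hoc stage can rescue the branch. A reader might infer from the lack of a difference-of-changes pair that Dunn's test cannot answer the treatment question. The article does not support that. With all six orders counterbalanced within patients, before-block scores have equal expectation across conditions unless carry-over differs, so active-after versus sham-after is a valid treatment contrast, and it is among the 15 pairs. It also has power: for a true effect of 0.75 SD in one arm and a shared gain of 0.5 SD at n=36, it detects 65% unadjusted and 27% with Bonferroni, against 48% for the omnibus Friedman test on changes. This stands. What remains is that section 2.9 does not single out this pair, and the omnibus test and the before/after pairs carry the problem.

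A reader might also infer ten practice runs at each assessment and hence a sure gain. Section 2.4.1 says "patients will be trained to perform the test for five consecutive trials", but not that the training is repeated at all six assessments, and unrecorded training would tend to reduce the gain in the recorded trials. The size of any gain is unknown. Training would not, however, remove a placebo response.

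Third, this is one branch of two. The ANOVA branch contains the interaction, and nothing shows how likely the Friedman branch is for the primary variable. This also stands, though section 2.9 does not name the interaction as decisive there either. A loss of power from adjusting all 15 pairs should not be charged to the plan, which states no adjustment.

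Finally, the discussion calls the study exploratory. It does so to justify leaving out long-term assessment; the trial still has a primary outcome and a significance threshold. An unseen analysis plan could name the deciding contrast, but the six-cell Friedman test is stated here, not left open.

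**Conclusion.** The Friedman branch is wrong as written for a sham-controlled comparison of change. Its omnibus test can be significant with no stimulation effect, at rates from about 7% to 97% (n=36) or 99% (n=48) for shared gains of 0.1 to 0.75 within-patient SD. These rates depend on an assumed gain and variance structure that the article does not supply. With no shared gain the test holds about 5%, and learning from block to block alone does not inflate it.

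The conclusion does not extend to the ANOVA interaction or to active-after versus sham-after comparisons. Nor does it show that the trial will report a false effect: that needs the Friedman branch to be taken, a shared gain to exist, and the omnibus result or a before/after pair to be read as efficacy. The same wording covers the secondary outcomes measured on both D1 and D5. It cannot apply to the CGI and the CRQ, which section 2.5 lists only after D5.

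**What to change.** In section 2.9:

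- Form D5 minus D1 within each block and name the condition effect on that change (the time-by-condition interaction) as the single primary test.
- For a rank version, replace the six-cell Friedman test with Friedman on the three within-block changes. Follow it with signed-rank tests of two contrasts of change, motor minus sham and cerebellar minus sham, with Holm adjustment in place of Dunn's pairs.
- Choose the method for the 9-HPT in advance rather than by a normality test on the trial's scores.

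This costs a rewording of section 2.9, with no new data and the same software. Some power may be lost against an after-only contrast, because change scores carry baseline noise. Ranking changes on the ordinal scales (MAS, MRC) is itself imperfect, so for those outcomes the choice deserves a sentence of justification.
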